**Sensor data: to be used to calculate estimation algorithm**		
	Sleep pattern	Monitored using a cardiac activity sensor and the Fitbit watch given to participants at the initial visit
	Rapid eye movement (REM) sleep time	Monitored using the Fitbit motion sensor and cardiac activity sensor
	Heart rate	Monitored using the Fitbit sensor
	Step count	Monitored by compiling each participant’s daily step count using an accelerometer, smartphone GPS services, and Fitbit motion sensor
	Distance travelled	Monitored using the GPS services of each participant’s smartphone via the HumanITcare app
	Mobile device usage	Monitored by determining the time frames in which there was a presence or absence of signals from each participant’s device via the HumanITcare app
	Sociability: number of incoming and outgoing calls and text messages	Monitored by the number of incoming and outgoing calls and text messages from each participant’s smartphone via the HumanITcare app
**Questionnaire data: to be tested against estimation algorithm**		
	Self-reported anxiety symptoms	Assessed via the State-Trait Anxiety Inventory (STAI); participants receive STAI scores ranging from 0 (lowest number of symptoms) to 60 (greatest number of symptoms), which are then transformed into percentiles according to age and sex
	Self-reported depression symptoms	Assessed via the Beck Depression Inventory-II (BDI-II); participants receive BDI-II scores ranging from 1 to 63: a score of 0-13 indicates minimal depression, 14-19 indicates mild depression, 20-28 indicates moderate depression, and 29-63 indicates severe depression
	Self-reported alcohol use symptoms	Assessed via the Alcohol Use Disorders Identification Test (AUDIT); participants receive AUDIT scores ranging from 0 to 40: a score of ≥8 is associated with harmful or hazardous drinking and a score of ≥13 in women or ≥15 in men is likely to indicate alcohol dependence

#### Secondary Outcome: System Usability

Satisfaction with and usability of the data collection app will be evaluated after the trial period in order to determine the practicality of the user interface and to determine the practical feasibility of widespread usage of similar apps:

Satisfaction with the app will be scored using the PSSUQ [18]. Scores range from 0 (least satisfactory) to 100 (most satisfactory). Participants will be asked to complete the PSSUQ after the data collection period is over.Usability of the mobile app will be scored using the SUS [17]. Scores range from 0 to 100, with a score of ≥68 being considered above average. Participants will be asked to take the SUS after the data collection period is over.

### Data Collection, Management, Security, and Ethics

Treatment, communication, and transfer of personal data of all participants will be adjusted to compliance with the EU Regulation 2016/679 of the European Parliament and of the Council of 27, April 2016, on the protection of individuals with regard to the processing of personal data and the free movement of data. The legal basis that justifies the processing of data is the consent hereby given, pursuant to the provisions of Article 9 of EU Regulation 2016/679.

The data that will be collected from each participant are identified only by a randomized 8-digit code, so they will not include any information that could identify participants. Only the research team members with the right of access to the source data (ie, medical history) may relate the data collected in the study with the clinical history of the patient. The identity of participants will not be available to any other person except for a medical emergency or legal requirement. The Ethics Committee for Research, health authorities, and the personnel authorized by the study sponsor will have access to identifiable personal information when necessary to check data and study procedures but will always maintain confidentiality in accordance with current legislation. Moreover, the project will be conducted in accordance with the Declaration of Helsinki (2013).

### Risk Management Protocol

#### Stage 1: Recruitment

Table 2 shows the factors and challenges associated with participant recruitment, for both the experimental and control groups.

#### Stage 2: Initial In-Person Visit

Table 3 shows the factors and challenges associated with activities of the in-person visit.

#### Stage 3: Monitoring

Table 4 shows the factors and challenges associated with activities during the study duration and symptom monitoring.

#### Stage 4: Second In-Person Visit

Table 5 shows the factors and challenges associated with activities of the second in-person visit.

#### Stage 5: Analysis and Results

Table 6 shows the factors and challenges associated with study analysis and results.

**Table 2 table2:** Difficulties associated with participant recruitment and their correction measures.

Study activity and associated difficulties or risks		Measures to correct or mitigate
**Patient recruitment**		
	Low number of patients recruited or low involvement by health care professionals	Send weekly reminders
	Adult Mental Health Care Center professionals have little familiarity with the questionnaire	Attach the questionnaire in reminder emails for health care professionals
	Delay in the schedule due to slow recruitment	Expand to the maximum period of recruitment
**Control participant recruitment**		
	Low access to paired patient controls	Create database of potential candidates who wanted to participate as controls
	Dependence on the pace of patient recruitment	Provide informative brochures

**Table 3 table3:** Difficulties associated with activities of the in-person visit and their correction measures.

Study activity and associated difficulties or risks		Measures to correct or mitigate
**Presentation protocol and signing informed consent**		
	Participants decide not to participate	Summarize by phone so that they can assess whether to participate (avoid visit if uninterested)
	Participants do not understand the function	Explain in a simple and clear way the protocol and benefits (eg, “measure your sleep...”)
**Patient questionnaires**		
	Patients do not meet the inclusion criteria	Clearly specify the criteria and instruments when explaining the protocol and review medical history
**Download of the app**		
	Lack of storage space on phone	Forewarn the participant before the visit that an app will need to be downloaded
**Instructions of use**		
	Misuse of the app or device	Deliver a clear, visual instruction notebook in the first session Rehearse app use during the visit with patient Provide contact information to call in case of difficulties
**Explaining the follow-up**		
	Participants forget to respond to questionnaires	Prepare a specific calendar for the patients, showing schedule of days to respond to the questionnaires, and schedule a date for the second in-person visit
	Participants forget to wear the device daily	Send weekly reminders

**Table 4 table4:** Difficulties associated with monitoring during the study and related correction measures.

Study activity and associated difficulties or risks		Measures to correct or mitigate
**Correct use of the device**		
	No use	Send notifications encouraging use of the device Call to remind participants and stress the use of the device
	Problems with the server in recording of the data	Perform maintenance of the platform Call to record the daily use if more than 7 days without use
	Defective Fitbit	Provide contact number for technical problems Test devices in advance
	Forget username and/or password	Provide contact number in the instruction book for technical concerns Create database of patients and log-in data Configure the app so that it does not log out the participants
	Problems uploading the Fitbit data	Explain that Bluetooth needs to be enabled for uploading of data; participants should synchronize data every day
**Response to the weekly questionnaires**		
	No response	Send reminders in the form of notifications Review responses from the platform Consider a percentage of 30% as possible dropouts in recruitment
**Loss of the patient from the study**		
	No response to the calls	Consider a percentage of 30% as possible dropouts in recruitment
	Patients reject follow-up	Follow-up call to all patients in the middle of the study to explore difficulties and problems, to encourage, etc

**Table 5 table5:** Difficulties associated with activities of the second in-person visit and their correction measures.

Study activity and associated difficulties or risks			Measures to correct or mitigate
**Visit**			
	Forget to visit	Send reminder call before visit	
**Satisfaction and usability evaluation**			
	Validity of questionnaires	Select valid instruments	
	Bias	Aside from the general questions, include questions according to the number of uses of the bracelet and app	
**Delivery and retrieval of wearables**			
	No return of the device	Stress the necessity of returning the device Communicate that the patient must pay the cost of the device	
	Return in bad condition	Instructions of use Damage will be assessed and, based on impact, the device will be paid for if it is in bad condition	

**Table 6 table6:** Difficulties associated with activities of study analysis and results and their correction measures.

Study activity	Difficulties and risks	Measures to correct and mitigate
Data analysis	Problems with sample variability	Perform preliminary analysis with half of patients Control patients according to degree of use (ie, group according to involvement: a lot, moderate, low, and null)
Dispersion of the results	Scientifically irrelevant data	Assess the usability and satisfaction with the intervention and degree of use Determine association between severity of symptoms and degree of use

### Data Analysis

#### Overview

For each participant, we will collect data through a Fitbit and smartphone device, as well as written data through the form of questionnaires. The devices will offer insight into the physiological responses and changes within participants, which provides a more objective side of the data. For example, the heart rate monitor will report the intensity of one’s heartbeat and could suggest symptoms of anxiety. Additionally, the smartphone GPS will report a participant's movement and, therefore, insight into one’s daily energy or lethargy.

The written responses through questionnaires will give a subjective account of the participants’ anxiety or alcohol use disorder symptoms. An example of this is the STAI, which asks for a scalar rating on one’s feeling of lethargy. Using the data from the Fitbit and smartphone devices, plus the data from the questionnaires, we will determine any correlation.

#### Statistical Methods

The statistical analysis will be carried out as described in this section. Data collected from Fitbit devices, smartphones, and surveys from both groups will be interpreted with descriptive statistics. For the entire group, including all experimental and control participants, the mean and median will be calculated to determine the central tendencies. Next, we will find the standard deviation and range of the data to determine the variability within the dataset. The same process will be done for each group—experimental and control—individually, for the purpose of between-group comparison. The data will also be split and compared based on the source of the data: device information versus survey information.

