### Outcomes

#### Primary Outcome: Sensor Data Accuracy and Efficiency

The symptoms of anxiety and alcohol use disorder presented to the research team will be derived from the algorithm calculated from data collected by the HumanITcare platform (ie, app) and the Fitbit devices. These symptoms will be compared with the diagnoses provided by the status quo, *gold standard* questionnaires—the STAI [13] and the DSM-5 [16]—to determine the feasibility and efficiency of using objective sensor data in place of the current subjective methods of diagnosing mental health disorders. This will be done in a two-step process: first, by determining the relationship between the individual types of data tracked by sensors (eg, distance traveled and sleep schedule) and levels of anxiety and alcohol use disorder symptoms as presented by the questionnaires; and second, by using a mathematical model to estimate questionnaire scores by solely using the data collected by sensors (see Table 1). The primary outcome will be the efficiency of the developed algorithm’s ability to predict disorder symptoms.

**Table 1 table1:** Data collection by sensors compared with questionnaires.

Type of data being collected		Method of data collection

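### Statistical Methods limits the analysis to descriptive summaries, which cannot produce the primary outcome of how well the sensor algorithm predicts symptoms

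*Protocol article*

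**What the plan says.** Statistical Methods opens with a statement of scope: "The statistical analysis will be carried out as described in this section". It then fixes the type of analysis: "Data collected from Fitbit devices, smartphones, and surveys from both groups will be interpreted with descriptive statistics". For centre, "the mean and median will be calculated to determine the central tendencies"; for spread, "we will find the standard deviation and range of the data to determine the variability within the dataset". These are computed for everyone and then for each group. One further step follows: "The data will also be split and compared based on the source of the data: device information versus survey information". The section names no method or measure for that comparison and points to no fuller plan.

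The section on the primary outcome asks for something else: "The primary outcome will be the efficiency of the developed algorithm’s ability to predict disorder symptoms". It sets out two steps. The first relates each type of sensor data to symptom levels. The second proceeds "by using a mathematical model to estimate questionnaire scores by solely using the data collected by sensors". The reference standards named there are the STAI and DSM-5 diagnosis. Table 1 also lists the BDI-II and AUDIT among the scores against which the algorithm will be tested. The Data Analysis Overview adds that any correlation between device and questionnaire data will be determined, without naming a type.

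On splitting the sample, the only statement is in Table 6, as a measure against sample variability: "Perform preliminary analysis with half of patients".

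**The concern.** Two parts of the article do not fit together. One defines the primary outcome as predictive performance. The other says that it describes the analysis, and what it describes cannot measure predictive performance. An analyst who followed Statistical Methods as written would have a descriptive table and no result for the primary objective.

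The gap matters more because of the design. There are about 60 people with four weekly records each, and a model is built after looking at sensors one by one. In that setting the estimate of accuracy depends heavily on who is used to build the model and who is used to score it, and the article does not state this choice. The study aims to judge whether sensor data are an accurate basis for diagnosis, and the Discussion says the sample could inform the size of a follow-up study. An optimistic figure would mislead on both.

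**Working it through.** **Step 1. What each listed analysis can deliver.** The plan states no power, error rate or performance target, so it has no figure of its own to reproduce.

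- Mean, median, SD and range describe one variable at a time. Two data sets can share all of these for step count and for STAI and yet have any correlation between the two, positive, zero or negative. No prediction error, R², sensitivity, specificity or AUC can be derived from them.
- Repeating them by group compares cases with controls on each variable. It does not estimate a questionnaire score from sensors.
- The device-versus-survey comparison is unspecified. It could be read as covering the primary outcome only by supplying a method that the section does not give.

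**Step 2. What depends on the unstated choice of validation.** Inputs from the article:

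- 60 participants, 30 per group (Study Objectives). One dropout leaves 59 (Discussion). The 30% allowance in Table 4 would leave 0.7 × 60 = 42.
- Seven sensor data types for the algorithm (count from Table 1).
- Four questionnaire evaluations per person over 1 month (Weekly Assessment section). The Abstract gives a 4-month period; more weekly records would make the effect in (c) larger.

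Assumed, because the article does not give them: a linear model with independent features, 7 to 50 candidate features, and the intraclass correlations (ICCs) below.

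*(a) Scored on the same people, no true signal, one record each.* The expected apparent R² with p predictors is p/(n − 1).

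- n = 60, p = 7: 7/59 = 0.119.
- n = 42, p = 7: 7/41 = 0.171.

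Simulation (400 runs per setting, n = 60), with any selection repeated inside ten participant-level folds:

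| Setting | Apparent R² | Cross-validated by participant | New people |
|---|---|---|---|
| 7 predictors, no signal | 0.12 | −0.20 | −0.15 |
| Best 7 of 28, no signal | 0.28 | −0.33 | −0.29 |
| Best 7 of 50, no signal | 0.34 | −0.39 | −0.33 |
| 7 predictors, true R² 0.30 | 0.37 | 0.15 | 0.19 |

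With n = 59 the values are almost the same. Validation by participant removes the optimism and lies slightly below the value in new people.

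*(b) Scored on other weeks of the same people, no true signal.* A 3-nearest-neighbour model with 7 features and 4 records per person, split by record, gave a mean correlation between predicted and observed scores of 0.08 with both ICCs at 0.5 and 0.54 with both at 0.8. Split by participant, it gave −0.02 and −0.03. The article mentions no such model; this shows only how strongly the result depends on the ICC.

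*(c) Weekly records treated as independent when sensors are related to scores.* With m = 4 records, the variance of the correlation is multiplied by 1 + (m − 1) × ICC(sensor) × ICC(score). The false-positive rate at nominal 5% is P(|Z| > 1.96/√factor).

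- ICCs 0.5 and 0.6: factor 1 + 3 × 0.30 = 1.90, rate 15.5%.
- ICCs 0.7 and 0.8: factor 1 + 3 × 0.56 = 2.68, rate 23.1%.
- ICCs 0.8 and 0.9: factor 1 + 3 × 0.72 = 3.16, rate 27.0%.

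**The case against.** The strongest reply is that this is a condensed article of a pilot study and that a full protocol or analysis plan may give the model, the measure and the validation scheme. That stands for the validation scheme: its absence is not an error in itself. It does not answer the conflict, because Statistical Methods says it describes the analysis and then gives one that cannot reach the primary outcome. Pilot status does not remove the need to report the stated primary outcome by a method able to estimate it.

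Three stronger readings are tempting, and the article does not support them.

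- A reader might infer that no predictive analysis is planned at all. Primary Outcome announces a model and the Overview announces a correlation. The fault is that Statistical Methods does not carry them forward.
- A reader might infer that model building and scoring use the same people, so that any reported accuracy will be inflated. The article says neither that they do nor that they do not. Inflation follows only from one of the choices left open.
- A reader might infer that the half-sample analysis leaks into the final evaluation. Table 6 offers it only against sample variability, and nothing says the algorithm is built or tuned on that half.

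It is also fair to say that the sizes rest on assumptions. With the seven data types of Table 1 entered once each, the null apparent R² is a modest 0.12. The larger values need more candidate features.

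**Conclusion.** The mismatch is firm and rests on the text alone: the summaries listed in Statistical Methods cannot produce the primary outcome defined under Primary Outcome. It should be corrected before the data are analysed. At publication the data were still being processed, so there was room to do so.

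The risk of optimism is conditional. If the model is scored on the people who built it and there is no true signal, apparent R² is about 0.12 (7 predictors) to 0.34 (best 7 of 50) at n = 60. If weekly records are treated as independent, about 15% to 27% of null sensor-score tests would be significant at nominal 5%. These figures are illustrations under the assumed linear model, feature counts and ICCs. They do not forecast the study's result, but they are reason enough to state the validation scheme next to the model.

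**What to change.** Keep the summaries as a descriptive table, overall and by group. Replace the device-versus-survey sentence with the two-step analysis already promised under Primary Outcome.

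1. **Relationships.** Relate each sensor measure to the weekly STAI, AUDIT and BDI-II scores with a model that allows for four records per person, for example a linear mixed model with a participant random intercept. State whether STAI enters as the 0 to 60 score or as the age- and sex-based percentile that Table 1 describes.
2. **Prediction.** Predict those scores, and case status by DSM-5 criteria, from sensors alone. Name the model. Report out-of-sample error and R² for the scores, and sensitivity and specificity or AUC for case status.
3. **Validation.** Use cross-validation by participant, with all weeks of a person in one fold. Repeat any sensor screening inside the folds, including any choice made in the half-sample preliminary analysis.
4. **Benchmark.** Set performance beside a no-sensor prediction, for example from age, sex and, for the scores, the first-visit questionnaire result.

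The cost is a revised paragraph and modest programming, with no new data. The downside is that reported accuracy may be lower than an unvalidated figure.

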## Results

The recruitment phase was completed in November 2019 and all the data were collected by the end of December 2019. Data are being processed; this process is expected to be completed by October 2020.

## Discussion

The study is focused on patients diagnosed with anxiety and alcohol use disorder, but participants are also monitored for depressive symptoms throughout the trial, although these were not part of the initial inclusion criteria. Including this data while interpreting results could be a potential confounding factor. However, we would like to emphasize that while we recognize that anxiety disorders and depressive disorders are not clinically synonymous, major studies strongly support the finding that there are high rates of comorbidity between the two. In one study, results showed that 67% of patients with a depressive disorder also had a current anxiety disorder and 75% had a lifetime anxiety disorder [19]. Harvard researchers Jukka-Pekka Onnela and John Torous conducted a similar study using participants diagnosed with major depressive disorder and reported “Patients in this study were not excluded due to comorbidity of additional illnesses,” such as anxiety [6]. Due to this evidence, we believe there is justification for using participants who have symptoms of both. To avoid confusion, future research should prescreen for anxiety as well as depression, and standardize the initial sample. Researchers may also decide to use anxiety and depression interrelated questionnaires, such as the Depression Anxiety Stress Scales (DASS), that take into account the comorbidity of the two disorders, rather than primarily depression-related (ie, the BDI-II) or primarily anxiety-related (ie, the STAI) surveys, in order to improve reliability and validity of patient measures.

A limitation to our study is the exclusive use of Android smartphones over iOS devices. This study was conducted at the beginning stages of our company’s development. At that stage, we did not have the iOS version of the HumanITcare app available. There exists a potential selection bias due to the accessibility and affordability of Android phones as opposed to iOS-based phones. Research shows that Android phones are generally more affordable and financially available to those with a lower socioeconomic status (SES) [20] and that there are higher rates of anxiety and depression present among lower SES populations, possibly due to inferior or limited medical treatment [21]. Thus, this technological criterion may create a biased sample based on SES and the subsequent mental health disorders precipitated by the living conditions of those within this SES. Future research should include a sample of both Android and iOS users to eliminate any confounding variables related to the accessibility of each smart device. Additionally, statistics given by GlobalStats StatCounter show that the mobile OS market-share ratio between Android and iOS is approximately 80:20 [22]. Future research might include a sample that uses Android and iOS devices proportionate to the use in the country to eliminate any confounding variables and to be more accurately representative of the population.

Another limitation might be reviews of usability and satisfaction confounded by factors such as age and familiarity. Prior to the start of the study, researchers ensured that participants understood the tasks and they supplied hard copies of instructions. Researchers from the Hospital Clínic de Barcelona were also present during the training for quality assurance. Nonetheless, it is possible that younger cohorts within the sample are more likely to positively review the usability and satisfaction based on the technological fluency of their generations.

An additional function that we might add in future studies is the ability for patients to manage their own data. We plan to eventually employ an open-database system in which patients can access their own stats and measurements. This may or may not influence the success of the intervention by allowing participants to take notice of their own behavior.

This study was created and conducted as a pilot study with the Hospital Clínic de Barcelona, with the purpose of exploring the feasibility of our approach. The small sample size could be used to calculate the sample size necessary for the most citable outcomes in a follow-up study. Future research will use a larger sample to improve ecological validity. The study experienced one dropout from the experimental group. All original participants remained from the healthy control group.

